## **4. General Considerations**

### **4.1 Timing of analyses**

The final analysis of primary objective will be performed when all subjects have completed T1 or dropped out prior to T1. Data should meet the cleaning and approving requirements and SAP should be finalised and approved.

The final analysis of other objectives will be performed when all subjects have completed T2 or dropped out prior to T2. Data should meet the cleaning and approving requirements.

The cleaning and approving requirements are

- all expected CRFs have been entered,
- all queries are resolved,
- all data are consistent,
- data is determined to be clean and
- the expected centre signatures have been applied

### **4.2 Definition of analysis sets**

This section is designed to identify the characteristics needed for inclusion in particular populations used in the analysis.

#### **4.2.1 Full analysis population**

The main outcome analyses will be based on the full analysis population. The full analysis population consists of all randomised subjects who signed informed consent. Subjects will be analysed according to the intervention group they were randomised to (intention to treat), irrespective whether the subjects complied to the use of the smartphone according to protocol.

[figure not shown]

#### **4.2.2 Per protocol analysis population**

The per protocol population consists of all subjects who adhere to the major criteria in the protocol and who have a cardiopulmonary exercise test (CPET) test with sufficient quality of tests at T0, T1 and T2. For the intervention group this implies subjects who complied with the use of the smartphone (use of the smartphone on at least 4 days per week with a minimum of 30 minutes of activity per day with a total registration of 150 minutes of activity per week during 21 weeks) during the first 6 months of the study.

Sufficient quality of CPET is defined as follows: identical protocol used in tests to be compared, respiratory exchange ratio (RER)  $\geq 1.1$  (or, if RER  $< 1$ , if delta between T0 and T1 and/or T2  $\leq 0.05$ ), and test duration  $\geq 4$  min (excluding warm-up), no signs of mask leakage or other equipment failure by visual inspection of CPET data.

#### **4.2.3 Safety population**

The safety population is equal to the full analysis population (section 4.2.1).

#### **4.3 Data review meeting**

No formal data review meeting is planned. Prior to the start of the analysis each subject's inclusion or exclusion status with regard to both analysis populations will be assigned on the basis of the criteria described in section 4.2.

#### **4.4 Interim analysis**

No formal interim analysis is planned.

#### **4.5 Subject disposition**

The number of subjects randomised, and of those who completed each of T0, T1 and T2 will be presented together with the number of patients in each analysis set. Numbers will be depicted overall and by intervention group.

[figure not shown]

## 4.6 Summary of study data

All continuous variables will be summarised using the following descriptive statistics: n (non-missing sample size), mean, standard deviation, median, Q1, Q3, minimum and maximum. The frequency and percentages (based on the non-missing sample size) of observed levels will be reported for all categorical measures. In general, all data will be listed, sorted by intervention group and subject, and when appropriate by visit number.

### 4.6.1 Demographic and baseline variables

Demographic and baseline variables will be summarised by intervention group and overall for subjects in the full analysis population and per protocol population. Age (years) will be summarised as continuous data. Gender (male vs female), ethnicity (Caucasian (Caucasian, North African, Turkish, Other Middle East), Negroid, Oriental (Pakistan/Indian, Eastern Asia) or Other), highest educational attainment (university, secondary/high school, primary school), currently employed (yes, unemployed, sick leave, early retirement for health reasons, retired), currently involved in volunteer work (yes/no), form of living (alone/not alone), habitat (urban/rural) will be summarised as categorical data. Anthropometric parameters and vital signs will be summarized as continuous data in a table including height (cm), weight (kg), body mass index (kg/m^2), waist size (cm), hip size (cm), waist/ hip ratio, sum of the 4 skinfolds (mm), % of body fat, and lean body mass (kg), and resting blood pressure (systolic and diastolic, mmHg). Index diagnosis, comorbidity, left ventricular ejection fraction (LVEF), time from index to start exercise program, baseline blood pressure, laboratory measurements and medication will also be summarised.

The summary statistics will be produced in accordance with section 4.6.

[figure not shown]

#### 4.7 Missing data

All collected data will be used in the data analysis, also data from the patient who discontinue the study until the time of study discontinuation. Missing data will be reported overall and by intervention and centre. We will describe patterns in missing data. We will analyse whether missing data are systematically different between both groups (*mCR* and control group) or whether they are related to baseline values or values on earlier time points. In case that the occurrence of missing values is systematically different between groups, or is related to other variables, multiple imputation methods will be used to calculate parameter estimates for sensitivity analysis.

#### 4.8 Subgroups

The following important demographic or baseline value defined subgroups are to be analysed for different effects.

- Age
- Gender
- Index event: CAD versus VHR
- Educational attainment: low versus medium/high
- Per protocol: yes versus no

Subgroup analyses will be exploratory.

[figure not shown]

## 5. Study objective 1

Joining the *mCR* programme results in a lesser loss or greater gain in  $VO_{2peak}$  in cardiac patients between T1-T0 and T2-T0 than not joining the *mCR* programme. Primary study endpoint is physical fitness.

### 5.1 Efficacy analysis of primary study endpoint

The primary efficacy analysis will compare the change in peak oxygen uptake ( $VO_{2peak}$ /kg) from baseline (T0) to the 6 months follow up (T1) between the intervention and control group in the full analysis set.

$VO_{2peak}$ /kg will be derived from CPET. Approximated  $VO_{2peak}$  will be calculated from 6MWT as described under the definitions (document "EU-CaRE & EU-CaRE RCT SAP definitions").

The primary endpoint is the change in  $VO_{2peak}$  level between baseline (T0) and at 6 months (T1). It will be tested whether this change is different in the *mCR* and the control group by means of linear mixed models with the intervention as a fixed effect. The effect of centre on the outcome is modelled with a random effect. In the analyses we will adjust for the baseline value of  $VO_{2peak}$ . The null hypothesis is that there is no difference in mean change in  $VO_{2peak}$  level between the randomised groups. The alternative hypothesis is that the mean change in  $VO_{2peak}$  level differs between the randomised groups.

A covariance structure will be selected from several plausible structures. The covariance matrix resulting in the lowest Bayesian information criterion (BIC) fit statistic will be chosen.

To assess, if the underlying assumptions behind the mixed-effects model analysis are fulfilled, we will investigate normal quantile plots of residuals, standardized residuals, and random effects.

The linear mixed-effects model approach handles missing data appropriately and therefore multiple imputation or other methods to handle missing data in regard to the primary outcome will not be used. If necessary, the outcome variable will be transformed to obtain a normal distribution.

[figure not shown]

In case the groups differ on baseline values or other possibly confounding variables, the difference in change in  $VO_{2peak}$  level between baseline and 6 months between the intervention groups will be tested by means of linear mixed models analysis with centre as a random effect in which we will control for relevant confounders by adding covariates to the model. We will conclude a statistical significant difference in change in  $VO_{2peak}$  level between the *mCR* and control group when the two-sided p-value of the test statistic after adjustment for confounders is less than 0.05.

All analyses of PP will be in parallel to the description of the above.

## 5.2 Analysis secondary endpoints

The secondary endpoint for objective 1 is the change in peak oxygen uptake ( $VO_{2peak}$  kg) from baseline (T0) to the 12 months follow up (T2) between the intervention groups in the full analysis set.

Differences between intervention groups in physical fitness from baseline (T0) to the 12 months follow up (T2) will be analysed in similar linear mixed model approach described in section 5.1.

All analyses of PP will be in parallel to the description of the above.

[figure not shown]

## 6. Study objective 2

Joining the *mCR* programme results in a smaller loss or greater gain in  $VO_{2peak}$  in cardiac patients between T2 and T1 than not joining the *mCR* programme.

Outcome is change in  $VO_{2peak}$  (T2-T1). Differences between intervention groups in  $VO_{2peak}$  will be analysed in similar linear mixed model like the primary outcome. It will be tested whether change in  $VO_{2peak}$  (T2 – T1) is different in the *mCR* and the control group by means of linear mixed models with the intervention as a fixed effect. The effect of centre on the outcome is modelled with a random effect. In the analyses we will adjust for the T1 value of  $VO_{2peak}$ . The null hypothesis is that there is no difference in mean change in  $VO_{2peak}$  level between the randomised groups. The alternative hypothesis is that the mean change in  $VO_{2peak}$  level differs between the randomised groups.

A covariance structure will be selected from several plausible structures. The covariance matrix resulting in the lowest BIC fit statistic will be chosen.

To assess, if the underlying assumptions behind the mixed-effects model analysis are fulfilled, we will investigate normal quantile plots of residuals, standardized residuals, and random effects.

Additionally, we will perform a mixed models repeated measures (MMRM) analysis with intervention effect and time points as fixed effect and centre as random effect and baseline value as covariate. When necessary the outcome variables will be transformed to obtain a normal distribution. The null hypothesis is that the outcome under study is the same at all-time points (T0, T1 and T2). The alternative hypothesis is that the outcome under study at least one of the time points differs from the others. A covariance structure will be selected from several plausible structures. The covariance matrix resulting in the lowest BIC fit statistic will be chosen. We will test for the interaction between intervention group and time in order to investigate whether the development of study parameters over time differs between the interventions. A two-sided p-value of less than 0.05 for will be considered to be statistically significant. If the results of the MMRM analysis are statistically significant, we will run post hoc tests to highlight where these differences occur, adjusting the p value for multiple comparisons using the Tukey procedure.

[figure not shown]

## 7. Study objective 3

Joining the *mCR* programme results in improved traditional risk profile (i.e. lipid profile, HbA1C, lean body mass, blood pressure) in cardiac patients in comparison to not joining the *mCR* programme after 6 (T1) and 12 months (T2).

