### 3. Sample size

In order to assess the effects on sustained physical fitness after participation in the *mCR* programme it was determined that an inclusion of 119 patients per group would be sufficient to examine the aim of this study. This is based on the expected difference in increase in  $VO_{2peak}$  level of 3.0 ml/kg/min at 6 months between the control and intervention group with an estimated standard deviation of 5 ml/kg/min in the intervention group and 6 ml/kg/min in the control group. Assuming 80% power and 5% two-sided significance level ( $\alpha=0.05$ ), the sample size ( $n$ ) required to achieve a probability of 80% of detecting a difference in an increase  $VO_{2peak}$  level between two independent groups is  $n=55$  per randomisation group. Since patients from different centres (countries) will be pooled in the analysis, we will apply an adjustment for dependency of the observations to calculate the sample size, based on an estimated intraclass correlation coefficient (ICC) for the study centres. The ICC is the proportion of the total variance which is between the centers rather than within centres. An ICC of 0.05 is used in the sample size calculations. After adjustment for the ICC the sample size is  $N=83$  per group. Based on 30% withdrawal we aim for a group size of  $n=119$  per randomisation group ( $n=238$  in total). Six centres will participate in the RCT so we will aim at including approximately 40 patients per centre. As this is a cooperative trial, centres may recruit more patients than this recruitment goal. When one centre starts to dominate enrolment however, recruitment might need to be capped. The total sample size ( $n=238$ ) would be sufficient to detect a clinically and physiologically relevant change in peak oxygen consumption, despite a 30% dropout.

[figure not shown]

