### *Outcomes*

#### Cardiovascular risk factor control:

- Changes in lipid profile (T1-T2)
- Changes in HbA1C (T1-T2)
- Changes in lean body mass (T1-T2)
- Changes in blood pressure (T1-T2)

The differences between the randomisation groups on the secondary continuous outcomes will follow the same approach as described in section 6 Study objective 2.

All analyses of PP will be in parallel to the description of the above.

[figure not shown]

## 8. Study objective 4

The overall occurrence of MACE (cardiovascular mortality, all-cause mortality, near sudden cardiac death, ACS, CV intervention/surgery, CV hospital admission, CV emergency visit) in the intervention group is lower than in the control group at T1 and T2.

The cumulative incidences of the composite endpoint MACE and the elements from which it is constituted will be presented by group. We will compute the probability of survival free from MACE past given time points (6 months and 12 months) and the survival function will be plotted by intervention group in Kaplan-Meier survival curves. The Kaplan Meier curves will indicate the occurrence of MACE during 12 months of follow-up. Patients who do not experience an event or are lost to follow-up without an event are censored. We will test for differences in hazard rates between the *mCR* and control group using Cox regression analysis allowing the baseline hazard functions to differ between centres.

[figure not shown]

## 9. Study objective 5

Joining the *mCR* programme results in an improved general health (e.g. quality of life (SF-36v2: Physical and Mental Component Summary Score), level of depression (PHQ-9), level of anxiety (GAD-7) and dietary pattern (Mediterranean Diet Score)) in comparison to not joining the *mCR* programme after T1 and T2 in cardiac patients.

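### SAP section 6 tests the T2-T1 change in VO2peak while adjusting for the T1 value, an outcome of treatment, so it does not test its stated null hypothesis

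*Combined protocol and SAP*

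**What the plan says.** SAP section 6 (Study objective 2) takes the T2-T1 change in VO2peak as outcome and compares the arms "by means of linear mixed models with the intervention as a fixed effect", with centre as a random effect. It then adds: "In the analyses we will adjust for the T1 value of" VO2peak. The null is stated as equality of the arms: "The null hypothesis is that there is no difference in mean change in" VO2peak between the randomised groups.

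The same section adds an MMRM with arm and time point as fixed effects, "centre as random effect and baseline value as covariate". Its stated null concerns time: "The null hypothesis is that the outcome under study is the same at all-time points (T0, T1 and T2"). An arm-by-time interaction is also tested, and Tukey post hoc comparisons follow only if the MMRM is significant. The SAP does not say which analysis decides objective 2.

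SAP section 7 (Study objective 3) lists T1-T2 changes in lipids, HbA1c, lean body mass and blood pressure, which "will follow the same approach as described in section 6 Study objective 2".

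Protocol section 9.3 plans a baseline-adjusted MMRM for outcomes over time and has no T1 covariate. SAP section 18 does not list the T1 adjustment as a change.

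**The concern.** The primary model adjusts the T1-T0 change for T0. That is sound, because T0 precedes randomisation and the arms share its expected value. Section 6 moves the same step forward one visit, where the condition fails: T1 VO2peak is what the intervention is meant to change.

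Adjusting for T1 compares mCR and control patients of equal fitness at month 6. If mCR works, those patients are not alike, because the control patient is high within the control arm and the mCR patient is not equally high within the mCR arm. Regression to the mean then pulls the control patient down further. The model reads this as a benefit of mCR after it has stopped.

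At stake is the conclusion on what happens once telemonitoring is withdrawn. A gain that is simply held can be reported as a further gain, and waning can be understated or hidden.

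**Working it through.** **Inputs.** SAP section 3 gives an expected arm difference "level of 3.0 ml/kg/min at 6 months between the control and intervention group" and a "standard deviation of 5 ml/kg/min in the intervention group and 6 ml/kg/min in the control group". It also gives two-sided alpha 0.05, 80% power and 83 per group before the 30% withdrawal allowance. The T1-T2 correlation r is not in the documents, so a range of 0.5 to 0.9 is assumed. With equal T1 and T2 variances, b = r.

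**The plan's own figure.** The mean variance is (25+36)/2 = 30.5, so the SD is 5.52. Then n = 2 x (1.960+0.842)^2 x 30.5/9 = 53.2, or 54 by the normal approximation. The exact t calculation gives 55 (power 80.6%), as stated. 83/0.70 = 118.6, or 119, also as stated. The documents give no power figure for objective 2.

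**The shift.** Let D be the true arm difference in mean T2-T1 change and d the arm difference at T1. Within an arm, T2-T1 has slope (b-1) on T1. The T1-adjusted arm coefficient is therefore

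D - (b-1)d = D + (1-b)d.

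With D = 0 and d = 3.0 it equals 3.0(1-r): 1.5, 0.9, 0.6 and 0.3.

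**False-positive rate.** For level SD s and 83 per arm,

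SE = s x sqrt(1-r^2) x sqrt(2/83) x sqrt(1 + d^2/(4s^2)).

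Example, r = 0.7 and s = 5.52: 3.94 x 0.155 x 1.036 = 0.634. The shift over its SE is 0.9/0.634 = 1.42, which gives p<0.05 in about 29% of trials.

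The 5 and 6 can also be read as SDs of change, since they accompany a difference in increase. Applying that SD to T2-T1, the level SD is 5.52/sqrt(2(1-r)): 5.52, 7.13, 8.73 and 12.35.

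| r | Shift (ml/kg/min) | SE, SD of levels | Rejection | SE, SD of change | Rejection |
|---|---|---|---|---|---|
| 0.5 | +1.5 | 0.769 | 49% | 0.769 | 49% |
| 0.7 | +0.9 | 0.634 | 29% | 0.808 | 20% |
| 0.8 | +0.6 | 0.533 | 20% | 0.825 | 11% |
| 0.9 | +0.3 | 0.387 | 12% | 0.842 | 6% |

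Simulated trials agree. Under the first reading they gave 49-50%, 28-31%, 19-21% and 12-14%. Under the second they gave about 49%, 20%, 11-13% and 6-7%. Without the T1 covariate, the mean estimate was about 0 and rejection was 4.9% to 5.5%.

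**Waning (d = 3.0, r = 0.8, SD of levels).**
- 20% of the gain lost: D = -0.60, and the adjusted estimate is -0.60 + 0.60 = 0.00, so the loss disappears.
- Half lost: D = -1.50, and the adjusted estimate is -0.90. Power to see the loss falls from about 79% to about 39%.
- All lost: D = -3.0, and the adjusted estimate is -2.4.

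**Other T1 differences.** With d = 1.5 the shift is halved. With d = 0 there is none. With d = -3.0 and r = 0.8 it is -0.60, against mCR.

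**The case against.** **Sustained effect is not lost.** A reader might infer that the trial's sustainability conclusion is compromised. The documents do not support that. Protocol section 9.3 defines sustainable effectiveness by the change from T0 to T2. That comparison belongs to objective 1 (SAP section 5.2) and adjusts for a true baseline. Objective 2 is one secondary contrast. This stands and limits the reach of the point.

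**The MMRM already tests the arms.** It has no T1 covariate and includes an arm-by-time interaction, so it would be wrong to say that it addresses time only. Its T2-T1 arm contrast, if fitted, is free of this bias. It still does not cure the stated test, for four reasons:
- It is only additional, and no rule makes it decisive.
- Its interaction spans T0 to T2, so a T1 effect that is fully held can make it significant with no T2-T1 difference.
- The T2-T1 contrast is reached only through conditional Tukey comparisons.
- T0 is named as a time point and is also the covariate.

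A further inference, that this double use of T0 costs precision for objective 2, fails: the variance of the T2-T1 contrast without T0 adjustment was 0.99 to 1.01 times that with it, under exchangeable correlation.

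**The direction is not fixed.** The bias favours mCR only if mCR leads at T1 and b is below 1. This stands, although an mCR lead at T1 is the planning assumption.

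**The error rates depend on assumptions.** The correlation is not given and the SD can be read in two ways. This stands, so both readings are shown. The shift in ml/kg/min depends only on d and b.

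**Objective 3 is not quantified.** The documents give no expected T1 effect for the risk factors, so neither the size nor the direction of bias can be stated there.

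**Conclusion.** Wrong as written. The T1-adjusted model does not test the null of no difference in mean T2-T1 change; it is displaced by (1-b) times the arm difference at T1. On the plan's expected 3.0 ml/kg/min and a retained gain, the displacement towards mCR is 0.3 to 1.5 ml/kg/min for correlations from 0.9 down to 0.5. The false-positive rate then runs from about 12% to 49% if the planning SD is that of levels, or from about 6% to 49% if it is that of change. Waning is understated by the same displacement.

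This rests on 83 evaluable patients per arm, equal T1 and T2 variances and an assumed correlation. The flaw reaches secondary objective 2 and, by cross-reference, the T1-T2 risk-factor changes in objective 3. It does not reach the primary T1-T0 analysis or the T2-T0 analysis.

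**What to change.** 1. In SAP section 6, delete the T1 covariate from the T2-T1 model. This alone restores about 5% error.
2. Name one deciding test for objective 2: the arm effect at T2 minus the arm effect at T1, from a longitudinal model with T1 and T2 as the responses, arm, visit, arm-by-visit, the T0 value as covariate and centre as random effect. T0 is then no longer both response and covariate.
3. State the null as no arm-by-visit interaction between T1 and T2.
4. Make the same change for objective 3 in SAP section 7, and record the departure from protocol section 9.3 in SAP section 18.

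The choice of covariance structure and a T0-by-visit term are optional; neither is needed to remove the bias. The cost is SAP wording and a small change to the program. No new data, visits or patients are needed, because T0, T1 and T2 are already collected and a longitudinal model is already planned.

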## 1.6 Study schedule

All patients will have a follow-up after 6 months and at 12 months after the randomisation. Measurements will be performed at T0 (baseline), T1 (6 months after randomisation), and T2 (12 months after randomisation), see figure 1.

[figure not shown]

Figure 1. Study design EU-CaRE RCT

[figure not shown]

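### The additional MMRM picks its covariance by lowest BIC from unlisted structures; with at most three visits, an unstructured matrix should be prespecified, and the role of T0 stated

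*Combined protocol and SAP*

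**What the plan says.** SAP section 6 gives objective 2 two analyses. The first is a linear mixed model on the single change T2-T1, with centre random: "In the analyses we will adjust for the T1 value of" VO2peak. The second is extra: "Additionally, we will perform a mixed models repeated measures (MMRM) analysis". For that model the candidate structures are not named, and the rule is: "The covariance matrix resulting in the lowest BIC fit statistic will be chosen". No fallback order is given, and an unstructured matrix is neither named nor excluded.

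The MMRM text describes T0 in two ways. Its null hypothesis makes T0 an outcome visit: "The null hypothesis is that the outcome under study is the same at all-time points (T0, T1 and T2". Its model has "centre as random effect and baseline value as covariate", which normally means that only T1 and T2 are responses.

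Section 7 (lipids, HbA1C, lean body mass, blood pressure) "will follow the same approach as described in section 6 Study objective 2", so it takes over both analyses. Section 9 (general health) refers to section 5 instead and does not inherit the MMRM.

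The selection rule also stands in the single-change models. For the primary endpoint, SAP 5.1 states: "A covariance structure will be selected from several plausible structures". SAP 5.2 follows 5.1 by reference, and the first model of section 6 repeats the rule. Protocol 9.3 describes the MMRM without naming a covariance structure.

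**The concern.** Choosing a covariance structure from the data is worth the trouble when there are many visits and few patients. Here there are three visits at most. BIC charges the logarithm of the sample size for each parameter, so it favours compound symmetry, AR(1) or Toeplitz unless the data contradict them strongly. The model-based standard errors are then computed as if the chosen structure were true.

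Compound symmetry, AR(1) and Toeplitz all force the T0-T1 and T1-T2 correlations to be equal. For most entry routes T0 lies within three months of an acute event or procedure, whereas T1 to T2 is a later period without intervention, so equality cannot be taken for granted. If it fails, the standard error of one change is too small and that of another too large.

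At stake are the p-values of the MMRM for objective 2 and for each risk factor under objective 3. The open candidate list also means that nobody can tell beforehand which model will produce them.

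**Working it through.** **Inputs.** Three visits (SAP 1.6). SD of change 5 and 6 ml/kg/min, 80% power, two-sided 5%, and 83 per group after the ICC adjustment, before 30% withdrawal (SAP 3). The documents give no visit SDs, no between-visit correlations, and no effect size for T2-T1. Those are assumptions below.

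**The plan's own figure.** n = (1.960 + 0.842)² × (25 + 36) / 3.0² = 53.2, so 54 per group; the exact t calculation gives the stated 55. Also 83 / 0.70 = 118.6, so 119. These concern T1-T0 only. The plan states no power or standard error for the MMRM.

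**What BIC demands.** With 2 × 83 = 166 patients the penalty is ln(166) = 5.11 per parameter. With three responses, unstructured has 6 parameters, Toeplitz 3 and compound symmetry 2. Unstructured must therefore improve -2 log-likelihood by 3 × 5.11 = 15.3 over Toeplitz, or 4 × 5.11 = 20.4 over compound symmetry, to be chosen.

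**T0 as a response: closed form.** With equal variances, the variance of a change is 2σ²(1 − ρ). If the fitted correlation is ρ_f and the true one ρ, then

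reported SE / true SE = √[(1 − ρ_f) / (1 − ρ)].

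*Case A, T1-T2 most correlated:* T0-T1 0.60, T1-T2 0.70, T0-T2 0.55. Toeplitz averages the adjacent pairs to 0.65.
- T1-T0: √(0.35/0.40) = 0.935. The nominal 1.96 acts as 1.833, so type I error is 6.7%.
- T2-T1: √(0.35/0.30) = 1.080. The nominal 1.96 acts as 2.117, so type I error is 3.4%. Power designed at 80% becomes Φ(2.802 − 2.117) = 75%.

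*Case B, T1-T2 least correlated:* T0-T1 0.75, T0-T2 0.65, T1-T2 0.60. Compound symmetry averages to 0.667.
- T1-T0: √(0.333/0.25) = 1.155, type I error 2.4%.
- T2-T1: √(0.333/0.40) = 0.913, type I error 7.4%.

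The direction for T2-T1 has reversed.

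**T0 as a response: simulation with the BIC choice made in each trial.** 83 completers per arm, saturated arm-by-time means, REML, no centre effect, and candidates CS, AR(1), Toeplitz, heterogeneous CS, heterogeneous AR(1) and unstructured. There were 1,000 trials for each of seven assumed matrices (visit SDs 5 to 7, correlations 0.5 to 0.8).

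| Assumed pattern | T2-T1 SE, reported/true | T2-T1 type I error | T2-T1 power, BIC vs unstructured |
|---|---|---|---|
| T1-T2 most correlated | 1.02 to 1.09 | 3.1% to 4.2% | 2 to 5 points lower (e.g. 75% vs 80%) |
| T1-T2 not most correlated | 0.94 to 0.97 | up to 7.0% | no loss (82% vs 78-80%) |
| Compound symmetry true | 1.00 | no distortion | no loss |

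In the first row the T1-T0 SE was 2% to 5% too small, with type I error up to 7.4%. In case B it was 10% too large (type I error 3.2%). BIC chose unstructured in 0% to 77% of trials, depending on the matrix. Always fitting unstructured gave mean SEs of 0.996 to 1.002 of the true value. Monte Carlo error is about 0.7-0.8 points for type I error and 1.3-1.4 points for power.

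**Baseline as a covariate only.** The matrix is then 2 × 2, and CS, AR(1) and Toeplitz coincide. Unstructured estimates the variance of the difference as s₁² + s₂² − 2s₁₂. Compound symmetry uses the pooled variance: 2 × (s₁² + s₂²)/2 − 2s₁₂, which is the same number. With complete data the T2-T1 standard error does not depend on the choice. With about 30% dropout from 119 per arm, power differed by at most about 1 point. Only the visit-specific effects moved: the T1 SE was about 0-4% larger and the T2 SE about 0-3% smaller than under unstructured.

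**Single-change models.** One change per patient leaves no within-patient matrix to select, only a centre variance and a residual variance.

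**The case against.** The strongest reply is that this concerns an additional analysis. The test listed first for objective 2 uses a single change score, and the MMRM's pairwise comparisons are post hoc, run only after a significant result, and Tukey-adjusted. That stands, and it limits the point to the MMRM and the objective 3 analyses that inherit it.

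A reader might infer from the selection rule that objective 2 loses power. The documents do not support this. The loss needs T0 as a response and T1-T2 as the most correlated pair. The plan supplies neither the correlations nor a consistent statement on T0, and under other patterns the T2-T1 test is anti-conservative instead.

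It is also fair to say that BIC may select the unstructured matrix, and that a simpler structure does no harm when it is adequate. Both stand. They show that the harm is conditional, but they are no reason to keep a selection step that three visits do not need.

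The remaining wording in SAP 5.1 is largely harmless, because centre is already specified as a random effect there.

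**Conclusion.** The point holds as a low-cost improvement to the MMRM in SAP 6 and its use in SAP 7. If T0 is a response, BIC selection can give type I error of about 3-4% for one change contrast and 6-7% for another, with a T2-T1 power loss of about 2-5 points only when T1-T2 is the most correlated pair. If compound symmetry is true there is no loss, and if baseline is only a covariate there is almost none for T2-T1. The primary analysis and the change-score test of objective 2 are not shown to be affected.

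These sizes rest on assumed visit SDs and correlations, equal covariance in both arms, no centre effect, and a penalty based on the number of patients. The SAP does not say which count enters BIC: 498 observations (166 × 3) would give ln(498) = 6.2 per parameter and six centres ln(6) = 1.8, so the choice itself could change with that count.

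A reader might also infer that a wrong covariance shifts the point estimates under dropout. The documents give no basis for a size, and the calculations above did not measure it, so no such claim is made.

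**What to change.** - **SAP 6 (MMRM), and 7 by reference:** replace BIC selection with an unstructured within-patient covariance, fitted by REML with Kenward-Roger degrees of freedom. If it does not converge, use heterogeneous Toeplitz, then heterogeneous compound symmetry, in that order.
- **Same paragraph:** state whether T0 is a response or a covariate, and make the null hypothesis agree. Without this, unstructured could still mean a 2 × 2 or a 3 × 3 matrix.
- **SAP 5.1, 5.2 and the first model of 6:** as tidying, delete the covariance-selection sentence where it stands and describe a random centre intercept with one residual variance.

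The cost is a wording change through the SAP's own amendment route (section 15). It needs no new data and slightly less analysis work.
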